### Data analysis and variable definition

Data from different sources will be grouped according to the evaluation questions. This triangulation will allow validation of the information gleaned from the different sources. Regarding quantitative data, appropriate descriptive statistics will be used to present the results, i.e. means with standard deviations for normally distributed variables, median with inter-quartile ranges for variables not distributed normally, and proportions with 95% confidence intervals for categorical variables. These descriptive statistics will be of prime importance to assess conformity with accepted norms in the literature and norms considered acceptable for each target group and decision makers.

Subgroup analyses will be performed to compare for example utilization, satisfaction or perceived utility regarding optimal care delivery among different web-based tools; satisfaction of all participants regarding preceptorship, web-site and virtual community; scores on the different tests before and after preceptorship and after one year of utilization of web-based tools and virtual-community; etc. Sub-group analyses will be performed using ANOVA tests and repeated-measures ANOVA tests, with HSD Tukey multiple comparison tests.

Qualitative data will be analyzed using codification of all comments and information. Coded informations will be grouped under specific themes or concepts. Proportions of reported themes or concepts for each question or subject of discussion will be reported. These data will be particularly useful to develop and improve the program under objectives 1 and 2, and to assess pitfalls and strategies for implementation of the program in general settings (objective 5). Qualitative data are also of prime importance to interpret and understand results obtained from typical quantitative data, and generate hypotheses for future studies.

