### Participants

Under objectives 1 and 2: Development and implementation of a preceptorship, web site and virtual community, we first identified participating FMGs within the RUIS (clinical and teaching). A FMG was eligible to participate in the proposed study if at least one PCP and one nurse were interested. We plan to recruit a total of 8 FMGs; appropriate regional authorities have approved the proposed research project. For each identified FMG, PCPs and nurses will be informed of the study and invited to participate. All interested FMG team members will be recruited with a maximum of 6 participants per FMG, 48 participants being the capacity limit of our preceptorship program.

Upon recruitment, participants will complete a needs-assessment questionnaire regarding obesity management and be asked to identify their expectations. An additional questionnaire will review their past experience with respect to obesity management. Preceptorships will be based on the existing format, i.e. a combination of theoretical and practical CME, and will include common and nurse- or PCP-specific sessions.

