As soon as FMGs begin their participation, we will conduct a prospective evaluation of the implementation of the preceptorship and network system. Innovative web-based tools will be used for this purpose, as well as more traditional methods. Since evaluation is crucial to the applicability and transferability of results under objectives 4 and 5, decision-makers will be involved early and actively throughout the process. This should ensure that decision-makers are active members of the research team and as such increase the probability that they will use the study results.

Specific research tools for each objective are summarized in Table 1, which includes corresponding indicators and variables as well as the sources that will be used to obtain required data. We will not detail each of our methods in order to improve the readability of this paper. However, detailed methodologies will be made available to the reader on request by contacting the corresponding author.

**Table 1 T1:** Summary of Methodology and Approach

**Objectives**	**Indicators or variables**	**Sources**
**1. **Develop and implement a preceptorship-based CME for FMG teams	a. Perceived pitfalls to implementation of the program	• Focus groups
**2. **Set up aa a collaborative intra/inter-regional interdisciplinary network		
**3. **Evaluate implementation of this integrated obesity care system:		
**3a) **ability of preceptorship structure to train 8 FMG teams during the research program	a. Proportion of candidates who agree to participate b. Proportion who participates in the preceptorship c. Resources needed for each preceptorship	• Data from the regional health agency • Administrative data from the project team • Budget and administrative data from the project team

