**3b) **accessibility and utilization of the website and virtual community following preceptorships for FMG team members	a. Number of times participants access the website b. Length of time spent and the number of times individual tools are accessed c. Perceived utility of the tools in general d. Most helpful tools e. Obstacles and facilitating factors in using the website f. Resources needed to maintain the website g. Team members participation to the virtual community h. Degree to which the virtual community meets physicians' needs i. Resources needed to support the virtual community j. Degree to which participants perceived they achieve optimal obesity care delivery k. Perceived utility of each tools to optimal care delivery	• Web logging tools • Web-based questionnaires • Telephone and person-to-person structured interviews • Clinical vignettes and web-based learning tools • Web-based anonymous partial patient records • Budget and administrative data from the project team • Secondary care professionals' logbooks
**3c) **satisfaction of FMG team members and secondary care professionals	a. Participants expectations b. Participants satisfaction with the preceptorship c. Participants satisfaction with the website d. Participants satisfaction with the virtual community e. Suggested improvements by participants f. Secondary care team members satisfaction with preceptorship, web-site and virtual community g. Secondary care team members ease with this method of sharing expertise and patient care h. Suggested improvements by secondary care team members	• Traditional and web-based questionnaires • Telephone and person-to-person structured interviews • Focus groups with selected participants • Telephone and person-to-person structured interviews of secondary care team members • Focus groups with selected secondary care team members
**4. Assess the impact of the preceptorships and network system on obesity primary care delivery, related to participating FMG team members:**	Number of patients managed in the network	Web-based participants log-book
**4a) knowledge and expertise**	a. Score on test b. PCPs care practices c. Descriptive information on delivered care	• Pre-test and post-tests • Traditional and web-based questionnaires • Web-based anonymous partial patient records

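### Repeated-measures ANOVA with Tukey HSD suits three unequally spaced test scores poorly: in its classical form it discards incomplete participants and can mis-size individual contrasts

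*Protocol article*

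**What the plan says.** Under Data analysis and variable definition, the protocol article lists, as one example of its subgroup analyses, "scores on the different tests before and after preceptorship and after one year of utilization of web-based tools and virtual-community". It then states: "Sub-group analyses will be performed using ANOVA tests and repeated-measures ANOVA tests, with HSD Tukey multiple comparison tests". It does not say which listed comparison gets which test, but repeated-measures ANOVA is the natural reading for three scores from the same people.

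Table 1 (Research tools) gives "Pre-test and post-tests" as a source for objectives 4a (knowledge and expertise) and 4b (attitudes).

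The sample is set by capacity. Under Participants: "We plan to recruit a total of 8 FMGs", "with a maximum of 6 participants per FMG, 48 participants being the capacity limit of our preceptorship program".

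The article gives no rule for missing one-year scores, no sphericity check or correction, and no error term for the Tukey contrasts. It says that "detailed methodologies will be made available to the reader on request by contacting the corresponding author".

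**The concern.** Two properties of the named procedure matter here.

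- **Complete triplets.** Classical repeated-measures ANOVA needs all three scores from each person. Someone who sits the pre-test and post-test but not the one-year test drops out of the pre-post comparison too. That costs precision in a small study. It also biases the change if those who stay differ from those who leave.
- **One pooled error.** The classical within-subject Tukey HSD applies a single error term to all three pairwise contrasts. This is right when the differences between time points have equal variance (sphericity). Here two tests surround the preceptorship and the third follows a year of tool use, so equal correlations are unlikely. The contrast with the lowest correlation is then judged against too small an error, and the one with the highest correlation against too large an error.

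The pre versus one-year contrast shows whether a gain lasts. Post versus one year shows whether it fades. Patient outcomes are left to a later study (Discussion), so the test scores are among the main quantitative evidence for objectives 4a and 4b.

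**Working it through.** **Inputs from the article.** Three time points; 8 FMGs with at most 6 participants each, and 8 × 6 = 48, which agrees with the stated maximum. There is no power calculation to reproduce.

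**Assumed, because the article gives none.** SD 1 at each test, familywise alpha 0.05 two-sided, one-year loss 20 to 40%, and the correlations shown below.

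**1. Participants and precision.** With complete cases only, the pre-post SE is multiplied by √(48/n).

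| One-year loss | n analysed | SE factor |
|---|---|---|
| 20% | 38 | √(48/38) = 1.12 |
| 30% | 34 | √(48/34) = 1.19 |
| 40% | 29 | √(48/29) = 1.29 |

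**2. Bias when dropout depends on the post-test.** Let the log-odds of dropout fall by 1 per SD of post-test score. Numerical integration over a normal post-test gives the amount δ by which retained people's mean post-test exceeds the full-group mean: 0.173 SD at 20% loss and 0.332 SD at 40%. With joint normality, the retained people's pre and one-year means shift in proportion to their correlations with the post-test:

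- Bias of post minus pre = δ(1 − r[pre,post]).
- Bias of one year minus pre = δ(r[post,year] − r[pre,post]).

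| r[pre,post] / r[post,year] | Post change, 20% to 40% loss | One-year change, 20% to 40% loss |
|---|---|---|
| 0.5 / 0.7 | 0.087 to 0.166 SD | 0.035 to 0.066 SD |
| 0.7 / 0.7 | 0.052 to 0.100 SD | 0 |

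A separate simulation at 30% loss with both correlations 0.7 agrees: complete cases gave a post change of 0.88 against a true 0.80, and a one-year change of 0.51 against 0.50.

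**3. Error of each contrast.** With n = 48, the pooled error has 2 × 47 = 94 degrees of freedom and q(0.95; 3, 94) = 3.368. Tukey HSD therefore declares a difference when |t| exceeds 3.368/√2 = 2.381, with t computed from the pooled SD. Under sphericity this is 1.9% per contrast. Otherwise:

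- Pooled SD of a difference = √(2(1 − mean r)).
- True SD of that difference = √(2(1 − r)).
- Effective threshold = 2.381 × pooled/true.

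For pre versus one year:

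| r pre-post / pre-year / post-year | Pooled SD | True SD | Ratio | Effective threshold |
|---|---|---|---|---|
| 0.7 / 0.49 / 0.7 | √(2 × 0.370) = 0.860 | √(2 × 0.51) = 1.010 | 0.852 | 2.03 |
| 0.5 / 0.3 / 0.8 | √(2 × 0.467) = 0.966 | √(2 × 0.7) = 1.183 | 0.816 | 1.94 |

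For post versus one year in the second row, the true SD is √(2 × 0.2) = 0.632, the ratio 1.53 and the threshold 3.64.

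Simulated false-positive rates with no true change (n = 48, at least 20,000 runs each):

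- Equal correlations: about 1.9% per contrast, 5.0% familywise.
- 0.7 / 0.49 / 0.7: pre versus one year about 4.6%, familywise about 5.7%.
- 0.5 / 0.3 / 0.8: pre versus one year about 5.5 to 5.6%, post versus one year about 0.05%, familywise about 6.2%.

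If the high correlation of 0.8 falls on the pre-post pair instead, that is the contrast that becomes nearly undetectable (0.06%).

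**4. Effect of the alternative.** Paired tests at 0.05/3, each with its own error, held pre versus one year at 1.5 to 1.7% (target 1.67%) at n = 48. With 30% loss and adjacent correlations of 0.7, using all available scores gave a pre-post SE of 0.11 against 0.13 to 0.14 for complete cases. The one-year SE was 0.16 to 0.17 against 0.17 to 0.18.

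**The case against.** The article is condensed and refers readers elsewhere for detail. Handling of missing scores and of non-sphericity commonly belongs in a fuller document, so its absence is not a fault. This stands. The point is therefore about the method that the article does name, which a fuller document would have to override.

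The size can also be called modest. Tukey HSD is meant to control familywise error, which moves only from 5% to about 6%. The largest one-year bias, 0.066 SD, is about a third of its standard error at n = 29 (√(1.2/29) = 0.20 at an assumed pre-year correlation of 0.4). This also stands. What remains is that error is distributed unevenly among the contrasts and that usable scores are lost.

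A reader might infer that ordinary ANOVA will be applied to the repeated scores, with a large loss of power. The text does not assign it to them. The list is given by way of example and left open, and between-group comparisons are plausible: physicians and nurses have some separate sessions, and both FMG members and secondary care staff rate satisfaction.

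Finally, these tests do not carry objective 4 alone. Objective 4c is assessed qualitatively, 4a and 4b also draw on questionnaires and other sources, and the section gives descriptive statistics prime importance.

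**Conclusion.** The point holds as a weakness of the named method. In its classical form, repeated-measures ANOVA with Tukey HSD would discard usable pre and post scores from anyone without a one-year test. With dropout related to the post-test, it would also overstate the post change by roughly 0.05 to 0.17 SD at 20 to 40% loss. Under unequal correlations it can more than double the false-positive rate for pre versus one year, and can leave another contrast almost undetectable.

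Two stronger readings are not supported. The article does not say that incomplete participants will be dropped; that is the procedure's default. Nor is the Tukey error certainly wrong: it is correct under equal correlations, and failure of sphericity is likely but not established. Likewise, inflation of the one-year change is not inevitable: in the dropout model used here it vanishes when the pre-post and post-year correlations are equal.

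Every size above rests on assumed correlations, dropout rates and dropout mechanism.

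**What to change.** For the test scores, replace repeated-measures ANOVA with Tukey HSD by a linear mixed model (REML) fitted to all available scores, with time as a three-level factor and an unstructured within-participant covariance. Report pre versus post and pre versus one year as planned contrasts, Holm-adjusted, each with a 95% confidence interval. State that ordinary ANOVA is used only for between-group comparisons.

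The model keeps everyone's pre and post scores and gives each contrast its own error. It removes dropout bias only where the observed scores explain the dropout; if people leave for reasons that those scores do not capture, such as low engagement, some bias remains.

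The cost is a change of analysis wording and slightly more analyst time. No extra data are needed.

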### Significance, Impact and transferability

This research program will deliver transferable knowledge on management of obesity to primary care givers and will identify the potential pitfalls and strategies of setting up preceptorships and integrated interdisciplinary primary care team networks. Importantly, it will also yield important information on appropriate performance indicator sets for the future assessment of care access and delivery. The data derived from our study could be highly useful to health-system managers in Canada in order for them to implement truly integrated primary care delivery systems and programs targeting the obesity epidemic that we are facing. Date on financial and human resource requirements will be important for their planning.

The process and outcome measures are relevant and useful to a number of health system managers and policy makers. The *ADRLSSSS *of Estrie and Saguenay regions, as well as stakeholders from FMGs and the Public Health Directorate, will be actively involved in this research proposal. Our results will impact on the planning, allocation and management of resources as they apply to service organization. Early involvement of decision makers as co-investigators and active participants in our research project considerably increase the likelihood of implementation of changes in our health care system based on the outcomes of the present proposal. Research results are anticipated to be applicable to other institutions and regions of Quebec and Canada because most regions have access to specialists who could support networking with primary care teams. Our evaluation will also allow us to improve our program and, therefore, will also benefit our local health care system.

### Knowledge translation and transfer plan

It is worth mentioning that both the research program and the research design of this study are optimal to allow knowledge translation (KT) and application throughout the entire research process. Participants in the study will play an active role in validating the educational and clinical tools, discussing themes, applying new knowledge in their practice, and giving and receiving feedback during interdisciplinary and disciplinary team meetings and focus groups. Importantly, the preceptorship experience in itself is a knowledge translation activity for health professionals.

However, research by itself does little to induce change (except for participants) and thus, results have to be diffused to interested audiences. We have thus reserved a seven-month period exclusively aimed at knowledge transfer. We have access to specialized resources in communication from the Centre de recherché clinique Étienne-Le Bel to develop an optimal strategy based on KT literature [46-51].

Our research is relevant to: PCPs, nurse coordinators, specialists in various disciplines and associated health professionals, CME departments, public health directorates, health-system decision-makers. The research team members will thus reach out to these parties through linkage and exchange activities, including presentation of study results at scientific meetings and publication in scientific journals, but also by direct reports to decision-makers and health policy stakeholders. A clear summary of research results, including key messages targeted for each selected audience and synthesized results (divided by themes) will be made available in print and on a web site. Local media will be invited to a press conference. These approaches will first be pilot tested and should increase the use and widen the application of our results.

Our research team is composed of members that have preferred access to various interest groups. The decision-maker co-applicants will be instrumental in making contacts with other decision-makers at the provincial and national levels in order to eventually have an impact on health care organization. As already mentioned, the probability is high that our decision-maker co-investigators will appropriate and make use of the results of this study, because they will be involved early and actively in the research. Other members will easily reach specialists, primary care physicians, nurse-coordinators, public health stakeholders, CME departments and organizations; these interventions could impact obesity care delivery and CME delivery.

The results of this study will also be disseminated in medicine, nursing and other health professional discipline curricula to implicate them at an early stage in their training programs; Faculties of Medicine and Health Sciences will be invited to a web-based presentation of our results. The interdisciplinary-based practice that prevails in the study will be proposed to graduate students as an example of a methodological approach to program evaluation and implementation. Interest groups and community support group will also benefit from website conferences and workshops on the results of this study.

## Discussion

This project is relevant to health system's decision-makers who are confronted with an important increase in the prevalence of obesity. It is therefore critical to develop strategies allowing the management of obesity in the 1^st ^line setting. Results of this research project could therefore influence health care organization in the field of obesity but also eventually for other chronic diseases.

Should our data show that this integrated obesity care management system is effective in modifying short and long-term outcomes, future studies could concentrate on evaluating health indicators and patient satisfaction with such a system. The development of additional electronic tools for direct patient use may also turn out to be necessary. Other avenues of research include assisting other teams and decision makers in the implementation of similar programs or other research projects that will arise from our knowledge transfer activities.

In view of the limited resources (financial and time) available for the realization of the proposed project, we will not be able to measure the clinical outcomes of patients followed by the research participants. However, we view this application as a first step in the study of the impact of our integrated obesity care system on participating health professionals and their practice. Therefore the study of clinical outcomes of patients cared for by participants in a program, such as the one proposed here, compared to a control group of patients cared for by non-participating physicians, will be the object of a future and grant application.
